**Figure 2 F2:**
[figure not shown]
**Intervention Adoption Strategies to Support Implementation of Intervention Components.** Health Promoting School Intervention Components. Hypothesised Mediators. Behavioural Outcome.

### Intervention adoption strategies

The lack of explicit intervention adoption strategies has been highlighted as a limitation of school based physical activity interventions [13]. To increase the extent of school adoption of the intervention, seven strategies will be used to support implementation of the physical activity components. These strategies are based on literature shown to facilitate the adoption of school based interventions, change service delivery practices of organisations and build capacity of an organization [25,30,31,61-64]. These include:

1. *Change agent position* (*in**school physical activity consultant*): A Health and Physical Education teacher will be located within each school for one day per week over the intervention period to support the planning, and implementation of the program under the guidance of the school Principal and the Head Health and Physical Education teacher. This is consistent with previous research showing that location of a physical activity expert within a school can increase the amount of MVPA in Physical Education lessons [57].

2. *Establishing leadership and support*: A committee will lead and oversee the implementation of the intervention within each school. This role could be taken on by an existing school committee or a new school committee could be established with representatives from the school executive, health and Physical Education staff, staff from other key learning areas, students, parents and community. The committee, with the guidance of the in-school consultant will develop an intervention implementation plan. Meetings will be suggested to occur quarterly. Schools will also be asked to nominate a school co-ordinator whom the in-school consultant can work closely with for the duration of the project with the aim of handing over to this person when the research trial has been completed. Presentations will be given to all school staff in addition to the Health and Physical Education teachers and parents. These presentations will provide a means of gaining support for the project, providing input into the implementation and also inform the school community of progress. School Principals and Health and Physical Education head teachers will be encouraged to provide leadership via raising the program at staff meetings, attending the school committee meetings and approving and implementing supportive policy changes.

3. *Staff Training*: Training from credible professionals has been shown to be an effective implementation support strategy [18,61]. Teachers will be provided with training in the physical activity components relevant to their role in implementation. Health and Physical Education teachers will specifically be trained to deliver Physical Education lessons that increase students MVPA. Training and tips will be regularly provided by the in-school physical activity consultant and further professional development sessions will be held twice a year (4 sessions in total over the intervention). The training will be a series of practical learning workshops designed to foster skill development where schools can jointly share their experiences in implementing the strategies, rather than a didactic lecture style format. Teachers from across the whole school will also be invited and trained to deliver the enhanced school sports programs [48,52].

4. *Resources*: Schools will receive an intervention manual including material to implement the Physical Education lesson strategies, enhanced sports and physical activity programs during school breaks, and material on other strategies. Schools will also receive physical activity equipment such as elastic tubing resistance devices, pedometers, active electronic games consoles, skipping and boxing equipment. In addition to the resource kit provided to schools, additional small promotional incentives such as shirts and lanyards will be provided to teachers upon the introduction of curriculum based strategies. Small promotional incentives (balls, wrist bands, water bottles etc.) will also be given to students upon reaching their personal physical activity goals, for participating in recess and lunchtime activity and completing the enhanced school sports programs.

5. *Prompts*: The physical activity consultant will provide prompts such as emails, reminders in meetings and markings on calendars to teaching staff to undertake intervention strategies. The physical activity consultant will also work with schools to identify ways to build prompts into school communication processes and documents such as electronic calendar reminders and agenda items in meetings.

6. *Intervention adoption performance feedback*: Principals and Head Health and Physical Education teachers at each school will be given feedback on progress on each physical activity intervention strategy against agreed standards at the end of each school term (quarterly). The feedback reports will also include suggestions and offer support on how to improve performance.

### Control schools

Control schools will participate in the measurement components of the study only. Control schools will be offered one day of teacher relief funding at each data collection point (baseline, mid-point and follow-up) to reimburse the school for their time in assisting with data collection. Control schools will also be offered the physical activity equipment pack, all developed intervention materials and the results of the study at the end of the intervention period.

### Data collection procedures and measures

All data will be collected at three time points: baseline; 12- and 24-months. Students will wear an accelerometer to record physical activity levels, undertake an on-line survey, and have anthropometric measures taken. The accelerometers and instructions for use will be distributed to students at school within class time, at the same time as students complete the online survey and have anthropometric measures taken.

#### Outcome measure- physical activity levels

The primary outcome will be student physical activity defined as mean minutes of MVPA. Percentage of time spent in MVPA will also be calculated to adjust for individual accelerometer wear time.

Objectively measured physical activity data will be collected via accelerometers (Actigraph GT3X+ and GT3X model). Accelerometry provides an objective, valid and reliable way of measuring physical activity in young people [65-67]. Students will be asked by trained research assistants to wear the accelerometers during waking hours for seven consecutive days. The accelerometers will be attached to an elastic belt and worn over the right hip. Raw data will be collected and stored in 15 second epochs. Student data will be analysed if accelerometers are worn for ≥ 600 minutes on ≥ 3 days [68]. The Evenson cut-points will be used to categorize different intensities of physical activity [69]. Students will also be asked to keep activity monitoring logs for the seven-day period when the accelerometers were being worn. To improve compliance, students will be sent a text message each morning reminding them to wear the accelerometer [28,38]. Student and/ or parent mobile phone numbers will be requested via the consent form.

#### Student characteristics

An online survey, which will take approximately 30 minutes, will be undertaken to assess student socio-demographic characteristics (age, gender, Aboriginal or Torres Strait Islander status and postcode of residence), self-reported physical activity [70], physical activity mediators [28,71].

#### Anthropometric data

Anthropometric data including height and weight will be collected. Research assistants will be trained in measuring height, weight (used to calculate body mass index; BMI) and waist circumference using the International Society for the Advancement of Kinanthropometry (ISAK) procedures [72]. Weight will be measured in light clothing without shoes using a portable digital scale (Model no. UC-321PC, A&D Company Ltd, Tokyo Japan) to the nearest 0.1 kg. Height will be recorded to the nearest 0.1 cm using a portable stadiometer (Model no. PE087, Mentone Educational Centre, Australia). Waist measurement will be taken as the narrowest point between the inferior rib border and the iliac crest. Using a flexible but inelastic tape measure, the waist measure will be recorded to the nearest 0.1 cm. Two recordings will be taken and then the average will be used. The physical assessments will be conducted in a sensitive manner, with student measurements taken behind a privacy screen. Body mass index (BMI) will be calculated as weight/height squared (kg/m^2^). Weight status will be determined using International Obesity Taskforce definitions [73].

#### School outcomes/Process measures

Data regarding school policies and practices that enhance student physical activity will be collected at baseline and follow-ups via a school environment survey completed by the Head Health and Physical Education teacher at intervention and control schools. Based on existing surveys [74], the survey will focus on school policies and practices that enhance student physical activity including questions relating to school equipment and facilities, recess and lunch activities and rewards and punishments related to physical activity.

In addition, observational assessments of randomly selected Physical Education classes in both intervention and control schools will be undertaken at each time point to measure physical activity levels, lessons context and teacher interactions [75]. The observational tool, SOFIT (System for Observing Fitness Instruction Time), has been used in similar studies to assess physical activity levels in Physical Education classes [57]. Trained research assistants will conduct the assessments on the same weeks that student data collection is occurring.

Data will be collected by project staff throughout the intervention period to assess the extent of intervention adoption and implementation fidelity in intervention schools.

### Sample size

Based on an estimate of 50% of Year 7 students consenting and providing usable accelerometer data, each school should yield at least 60 students (based on at least 120 Year 7 students). This will provide at least 300 students per group. Based on an estimated 65% of the cohort providing usable data at follow-up, there will be at least 195 students per group at 24-month follow-up. Previous studies have been used to estimate the standard deviation of mean daily minutes MVPA per group (17.1) [28] and the Intra Class Correlation coefficient (ICC) (0.01) [76]. After adjustment for the design effect of 1.38, it is estimated the effective sample size will be at least 141 students per group. With this sample size, with 80% power and an alpha level of 0.05 the study will be able to detect a difference in the mean daily MVPA between experimental and control students of +/− 5.73 minutes at follow-up.

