### Statistical analysis – primary outcome

Analyses using cluster-level summaries are more robust than analyses based on individual-level data when there are less than 15 clusters per treatment arm [77]. Therefore the primary outcome for this study will be analysed by calculating the change in the mean number of minutes of moderate to vigorous physical activity within each school and then comparing the school-level means of the intervention group with the school-level means of the control group using a two sample t-test. The main analysis will be conducted with all available data using the intention to treat principle and sensitivity analyses conducted under various assumptions about the missing data mechanism [78]. Per protocol analyses will also be performed where appropriate.

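### The 80% power for 5.73 min/day is computed for a test with about 280 degrees of freedom; on the same inputs the planned t-test on 5 versus 5 schools (8 df) gives about 69%

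*Protocol article*

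**What the plan says.** The Sample size section of the protocol article starts from minimum numbers: "each school should yield at least 60 students" and, after 65% retention, "there will be at least 195 students per group at 24-month follow-up". It takes a "standard deviation of mean daily minutes MVPA per group (17.1" min/day) and an "Intra Class Correlation coefficient (ICC) (0.01") from previous studies. It applies a design effect of 1.38, from which "it is estimated the effective sample size will be at least 141 students per group". It concludes that "with 80% power and an alpha level of 0.05 the study will be able to detect a difference in the mean daily MVPA". The size it gives for that difference is 5.73 min/day in either direction.

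The section on statistical analysis of the primary outcome prefers cluster-level summaries because there are fewer than 15 clusters per arm. It computes the change in mean MVPA minutes within each school and then specifies "comparing the school-level means of the intervention group with the school-level means of the control group using a two sample t-test". The Abstract and the section on random allocation of schools give ten schools, allocated 1:1, so five per arm.

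**The concern.** The sample-size paragraph and the analysis paragraph describe different tests. The first treats the trial, once deflated by the design effect, as about 282 independent students. The second analyses ten school-level values.

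The two tests can share the same standard error, but they do not share a reference distribution. With ten values the between-school variance is estimated on 8 degrees of freedom, so a larger observed difference is needed for significance. The analysis paragraph recognises the small number of clusters; the power statement makes no allowance for it.

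At stake is a headline property of the design. A reader of a null result would take 5.73 min/day as a difference that the trial had 80% power to detect. On the protocol's own inputs the planned test does not provide that.

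**Working it through.** **Inputs**
- From the Sample size section: SD 17.1 min/day; ICC 0.01; at least 60 students per school at baseline; 65% with usable data at follow-up; alpha 0.05; power 80%.
- From the Abstract and the random allocation section: 5 schools per arm.
- Students followed up per school: 60 × 0.65 = 39, or 195/5 = 39.
- Sidedness is not stated in words. The plus/minus sign points to a two-sided test. A one-sided normal calculation gives 5.06, which does not match the printed figure.

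**Step 1: reproduce the protocol's figure**
- Design effect: 1 + (39 − 1) × 0.01 = 1.38.
- Effective sample size: 195/1.38 = 141.3 per group, printed as 141.
- Standard error of the difference: 17.1 × √(2/141) = 2.04 min.
- Two-sided t-test with 2 × 141 − 2 = 280 df (critical value about 1.97): the difference detectable with 80% power is 5.725, and power at 5.73 is 80.1%. A normal approximation gives 5.71.

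The printed 5.73 is therefore the individual-level result with about 280 df. Every step of the paragraph's arithmetic is right for that test.

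**Step 2: the planned test, same inputs**
- Variance of a school-level value: 17.1² × 1.38/39 = 10.35, so SD 3.217.
- Standard error of the difference between two means of five schools: 3.217 × √(2/5) = 2.034 min. This is the same standard error as in Step 1, so only the reference distribution changes.
- Degrees of freedom: 10 − 2 = 8; two-sided critical value 2.306.
- Power at 5.73, from the noncentral t with 8 df and noncentrality 5.73/2.034 = 2.82: 69.5%. A simulation of 400,000 trials gives 69.6%.
- Difference detectable with 80% power: 3.201 × 2.034 = 6.51 min/day, which is 0.78 min or 14% larger than 5.73.

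**Step 3: what this rests on**

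The planned test is on change, while 17.1 is given for mean daily MVPA. If the SD is the same at both times, the SD of change is 17.1 × √(2(1 − r)), where r is the correlation between a student's baseline and follow-up values. This equals 17.1 only when r = 0.5. The article gives no r. The values below are assumed to show the range, with ICC 0.01 and 39 students per school throughout.

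| Assumed r | SD of change | Power at 5.73 (8 df) | Detectable with 80% power (min/day) |
|---|---|---|---|
| 0.3 | 20.2 | 55% | 7.7 |
| 0.4 | 18.7 | 62% | 7.1 |
| 0.5 | 17.1 | 69% | 6.5 |
| 0.6 | 15.3 | 79% | 5.8 |
| 0.7 | 13.2 | 89% | 5.0 |

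The student numbers are also minimums. Eligible schools have 120 to 200 Year 7 students. At the same 50% and 65% rates, 160 per school leaves 160 × 0.50 × 0.65 = 52 followed up, and 200 leaves 65. With SD 17.1 and ICC 0.01, power at 5.73 with 8 df is then about 78% and 83%.

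**The case against.** A reader might infer that the trial's actual power is 69% and its type II error 31%. The documents do not support that, for two reasons. The planned test is on school-level change, and the article gives no SD or ICC for change; the table shows power from 55% to 89% over plausible-looking but assumed correlations. In addition, 39 per school is a floor, and larger schools would raise the figure. Both points stand, and they make the 69% conditional.

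Neither rescues the printed statement. The protocol attaches its 80% to the minimum of 141 effective students per group, so the comparison has to be made at that number. It uses 17.1 without any allowance for correlation, so a correlation slightly above 0.6, which would bring 80% back, is not among its assumptions. A one-sided test would give about 82% with 8 df, but it fits neither the plus/minus sign nor the value 5.73.

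It can also be said that the consequence is limited. The article names no minimally important difference, and 5.73 appears to be solved from a fixed ten schools. The validity of the t-test, its type I error and the confidence interval are unaffected, and a null result should be read from its interval. That is fair: the power statement needs correcting, but the analysis is not invalid.

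**Conclusion.** The power statement is wrong as written. It is a mismatch between the sample-size method and the planned analysis, not a slip in arithmetic. Moving from about 280 to 8 degrees of freedom, with everything else as the protocol states it, lowers power at 5.73 min/day from 80% to about 69% and raises the difference detectable with 80% power to about 6.5 min/day.

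These figures hold at the minimum student numbers, for a two-sided test, and if SD 17.1 and ICC 0.01 describe change as well as level. The power for change cannot be determined from the article. That the stated figure belongs to a different test does not depend on these conditions.

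**What to change.** Restate the sample-size paragraph for the test that will be run, and say which SD and ICC (or baseline/follow-up correlation) are assumed for change. For example:

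> Five schools per arm, at least 39 students per school at 24 months, two-sided two-sample t-test on school-level change with 8 degrees of freedom. Assuming an SD of change of 17.1 min/day and an ICC of 0.01, the trial has 80% power to detect 6.5 min/day (about 69% power for 5.73 min/day).

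If the sponsor has data supporting another correlation, quote the matching figure: with the ICC unchanged, about 7.7, 7.1, 5.8 and 5.0 min/day for correlations of 0.3, 0.4, 0.6 and 0.7.

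The cost is one paragraph and, unless a correlation above about 0.6 can be justified, a less favourable stated figure. The correction needs no extra schools and no change to the analysis. Recovering 80% power at 5.73 would be a separate design decision: on the same inputs, six schools per arm give about 79% and seven about 86%.

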### Statistical analysis – primary outcome

Analyses using cluster-level summaries are more robust than analyses based on individual-level data when there are less than 15 clusters per treatment arm [77]. Therefore the primary outcome for this study will be analysed by calculating the change in the mean number of minutes of moderate to vigorous physical activity within each school and then comparing the school-level means of the intervention group with the school-level means of the control group using a two sample t-test. The main analysis will be conducted with all available data using the intention to treat principle and sensitivity analyses conducted under various assumptions about the missing data mechanism [78]. Per protocol analyses will also be performed where appropriate.

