**Figure 1 F1:**
[figure not shown]
CONSORT flowchart describing progress of participants through the study.

The research will be conducted and reported in accordance with the requirements of the Consolidated Standards of Reporting Trials (CONSORT) Statement [32,33]. A randomly selected sample of disadvantaged secondary schools in the study region will be invited to participate. The schools will be randomly allocated to receive a multi-component intervention to be implemented during school terms and to commence after baseline data collection, or to a control group. Data will be collected from students at baseline (when students are in their first year of high school, aged 12–13 years), and from the same cohort of students after 12-months (midpoint) and 24-months post baseline data collection. The primary outcome will be minutes per day and percentage of time in moderate- to vigorous-intensity physical activity (MVPA) at 24-month follow-up.

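### The primary test uses unadjusted change in school means, but the 5.73-minute detectable difference is derived for an MVPA level; the two agree only at a baseline-to-24-month correlation of 0.5, and student-level baseline adjustment would be more efficient

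*Protocol article*

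**What the plan says.** The section Statistical analysis – primary outcome chooses school-level summaries because there are fewer than 15 clusters per arm. It specifies "calculating the change in the mean number of minutes of moderate to vigorous physical activity within each school" and then a two-sample t-test between arms on the school values. It names no baseline covariate, and it commits the main analysis to all available data under intention to treat.

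The Study design section defines the outcome as a level: "The primary outcome will be minutes per day and percentage of time in moderate- to vigorous-intensity physical activity (MVPA) at 24-month follow-up". The Sample size section also works with a level: "Previous studies have been used to estimate the standard deviation of mean daily minutes MVPA per group (17.1". It takes an ICC of 0.01 and continues: "After adjustment for the design effect of 1.38, it is estimated the effective sample size will be at least 141 students per group". On that basis it states a detectable difference at follow-up of 5.73 minutes, "with 80% power and an alpha level of 0.05". It uses neither an SD of change nor a correlation between baseline and follow-up.

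The Abstract and Background state the aim as reducing the decline in activity, which is a change concept.

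**The concern.** A change score fixes the coefficient on baseline at 1. If r is modest, subtracting baseline adds more noise than it removes, and the tested quantity has a larger variance than the one used for planning. The stated 5.73 minutes then belongs to a different analysis from the one that will be run.

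Baseline MVPA is due to be measured on the whole cohort. Using it as a covariate lets the data set the coefficient. With only ten schools precision is scarce, so giving some of it away through the form of the analysis matters more than it would in a large trial.

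**Working it through.** **Inputs from the article.** SD 17.1; ICC 0.01; 10 schools allocated 1:1; 60 students per school at baseline; 65% usable at follow-up, so 39 per school; alpha 0.05, taken as two-sided because the difference is given as plus or minus; power 80%. **Assumed:** the correlation r, which the article does not give, and equal variances at both times.

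**1. The plan's figure.** Design effect = 1 + (39 − 1) × 0.01 = 1.38. Effective n = 195/1.38 = 141.3 per group. Detectable difference = (1.960 + 0.842) × 17.1 × √(2/141) = 5.71 with normal quantiles, or 5.73 with t on 280 df. The stated figure is reproduced with 17.1 as the SD of a level and no correlation.

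**2. The same method applied to change.** SD of change = 17.1 × √(2(1 − r)), which equals 17.1 only at r = 0.5. With effective n 141 and normal quantiles:

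| r | SD of change | Detectable difference | Power at 5.73 |
|---|---|---|---|
| 0.2 | 21.6 | 7.22 | 60% |
| 0.3 | 20.2 | 6.75 | 66% |
| 0.5 | 17.1 | 5.71 | 80% |
| 0.7 | 13.25 | 4.42 | 95% |

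**3. The planned test, 5 v 5 schools on 8 df.** Between-school variance B = 0.01 × 17.1² = 2.924; within-school variance W = 0.99 × 17.1² = 289.49. With the same r for students and schools, the variance of one school's value is:

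- change, all available data: 2B(1 − r) + W(1/39 + 1/60 − 2r/60)
- change, students with both measurements: 2B(1 − r) + 2W(1 − r)/39
- mean residual after student-level adjustment: (1 − r²)(B + W/39)

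The standard error of the difference is √(2V/5), and power comes from the non-central t on 8 df.

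| r | V: all / completers / adjusted | Power at 5.73: all / completers / adjusted |
|---|---|---|
| 0.3 | 13.45 / 14.49 / 9.42 | 58 / 55 / 73% |
| 0.5 | 10.35 / 10.35 / 7.76 | 69 / 69 / 81% |
| 0.6 | 8.80 / 8.28 / 6.62 | 76 / 79 / 87% |
| 0.7 | 7.25 / 6.21 / 5.28 | 84 / 89 / 93% |

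For change on all data against adjusted, the detectable difference is 7.4 v 6.2 minutes at r = 0.3, 6.5 v 5.6 at 0.5 and 6.0 v 5.2 at 0.6. Student-level simulations agreed with these powers to about one point and put the type I error of the adjusted method between 4.2% and 5.7%.

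The textbook variance ratio of change to adjusted, 2/(1 + r), holds only for matched students. With 60 at baseline and 39 at follow-up the ratio is 13.45/9.42 = 1.43 at r = 0.3 (matched: 1.54) and 8.80/6.62 = 1.33 at r = 0.6 (matched: 1.25).

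**4. Sensitivity to stable schools.** Let the school-level correlation be 0.95 while students keep r. The school part of V becomes 2B(1 − 0.95) for change and B(1 + r² − 2r × 0.95) for adjusted. Power for change on all data against adjusted is then 73 v 79% at r = 0.3, 81 v 88% at 0.5 and 86 v 93% at 0.6, a gain of about 6 to 7 points.

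**5. A different form of adjustment.** ANCOVA on the ten school means has 7 df and must estimate its slope from ten points. Simulated power at 5.73 for completer change against this ANCOVA is 56 v 67% at r = 0.3, 70 v 75% at 0.5, 79 v 80% at 0.6, 89 v 88% at 0.7 and 97 v 95% at 0.8. Its advantage is gone above about 0.65.

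**The case against.** The strongest reply is that nothing here is invalid. Change matches the aim of slowing decline, and under randomisation change and baseline-adjusted follow-up estimate the same between-group difference. That stands in full. A reader might infer that the planned analysis is biased or aims at the wrong quantity; the article does not support this.

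A second reply is that every power figure depends on a correlation the article does not give. This also stands. Above r = 0.5 the change analysis is more precise than the planning variance, so one cannot conclude that using change leaves the trial short of power. Nor is there a fixed gain of 11 to 15 points: that range belongs to r of 0.3 to 0.6, equal correlation at both levels, and change on all available data.

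Third, the article does not call 17.1 a 24-month SD. It comes from earlier work with no time point given. That it describes a level follows from its wording and from the reproduction of 5.73.

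Fourth, the adjusted analysis needs both measurements on each student, whereas the plan promises all available data. This is a real, small cost.

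Finally, an unseen analysis plan may add adjusted models, so the absence of sex or other covariates is not a fault. The primary analysis itself, however, is fixed in the article.

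**Conclusion.** The point holds as a matter of efficiency and consistency. The 5.73 minutes is derived for a level, the primary test is on change, and the two coincide only at r = 0.5.

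Student-level adjustment followed by the same 8-df t-test had the higher power in every setting tried. Against change on all available data the gain is about 9 to 15 points for r from 0.3 to 0.7 with equal student and school correlation, and about 6 to 7 points if the school correlation is 0.95. Against change in completers it shrinks to about 1 to 4 points at a student correlation of 0.7 or more. The advantage belongs to this student-level form and should not be read as holding for any baseline adjustment.

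The fall from the stated 80% to about 69% at r = 0.5 comes from having 8 df instead of large-sample quantiles. It is a separate matter and is not caused by the choice of change.

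**What to change.** Make the primary analysis a two-stage cluster-summary comparison:

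1. Regress each student's 24-month MVPA on that student's baseline MVPA (sex optional), without the treatment term.
2. Average the residuals by school and compare the five intervention with the five control schools by the same two-sample t-test on 8 df.

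Keep unadjusted change on all available data as a sensitivity analysis. State the assumed baseline-to-24-month correlation with its basis, and restate the detectable difference for the adjusted analysis on 8 df.

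The cost is a change of wording in the analysis and sample-size sections. It needs no extra students or measurements, since baseline MVPA is already planned, and the cluster-summary approach is kept. The one trade-off is that stage 1 drops students without both measurements, so the plan should say how missing baselines are handled, for example by imputation.

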**Methods/Design:**

The cluster randomised trial will be conducted with 10 secondary schools located in selected regions of New South Wales, Australia. The schools will be selected from areas that have a level of socio-economic status that is below the state average. Five schools will be allocated to receive an intervention based on the Health Promoting Schools framework, and will be supported by a part-time physical activity consultant placed in intervention schools who will implement a range of intervention adoption strategies. Study measures will be taken at baseline when students are in Year 7 (12–13 years) and again after 12- and 24-months. The primary outcome, minutes of moderate- to-vigorous- intensity physical activity per day and percentage of time in moderate- to vigorous-intensity physical activity (MVPA), will be objectively assessed using accelerometers (Actigraph GT3x+). Group allocation and intervention delivery will commence after baseline data collection. The intervention will continue during school terms through to 24-month follow-up.

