#### Random allocation of schools

Eligible schools will be classified into two strata based on geographic location (regional or major city) [34]. Research indicates that location may contribute to the varying physical activity levels of adolescents [40]. Four consenting schools will be obtained from the major city strata and six from the regional school strata. Participating schools will be randomly allocated using block randomization (1:1 ratio) to the intervention or control condition using a computerized random number function. Randomization will be undertaken by a statistician not involved in contacting schools or in the study intervention or assessment and will occur after baseline data collection to reduce participation bias from students, teachers and researchers. The school Principal will receive a letter from the study team indicating to which group the school has been allocated. Data collectors will be blinded at baseline and where possible at 12 and 24-months data collection.

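### The primary t-test leaves out the location strata used in the randomisation; if city and regional schools differ in mean change, the test is mildly conservative, and one model term corrects this

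*Protocol article*

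**What the plan says.** On allocation (Protocol article, Random allocation of schools): "Eligible schools will be classified into two strata based on geographic location (regional or major city"). The reason given is: "Research indicates that location may contribute to the varying physical activity levels of adolescents". The numbers are fixed: "Four consenting schools will be obtained from the major city strata and six from the regional school strata". Then: "Participating schools will be randomly allocated using block randomization (1:1 ratio) to the intervention or control condition". Blocking within strata, and hence a 2:2 split of city schools and a 3:3 split of regional schools, is implied by this text but not stated; it is consistent with five schools per arm.

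On analysis (Statistical analysis – primary outcome), the endpoint is obtained by "calculating the change in the mean number of minutes of moderate to vigorous physical activity within each school" and the test consists of "comparing the school-level means of the intervention group with the school-level means of the control group using a two sample t-test". No stratum term, stratified test or within-stratum permutation appears there, and the Sample size section does not mention the strata.

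**The concern.** Stratified allocation removes the between-stratum difference from the comparison of arms. A two-sample t-test that ignores the strata still counts that difference as noise when it estimates the standard error. The reported interval is then wider than the design warrants, and the true type I error falls below the nominal 5%. With ten schools and 8 degrees of freedom there is little precision to spare. At stake are the width of the interval and some power, not the validity of a positive result.

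**Working it through.** **Inputs.** From Sample size: SD 17.1 min, ICC 0.01, design effect 1.38, 195 students per group at 24 months, detectable difference 5.73 min, 80% power, alpha 0.05 (two-sided, from the +/− sign). Five schools per arm gives 195/5 = 39 students per school. From Random allocation of schools: four city and six regional schools, taken as 2:2 and 3:3. Assumed: d, the city–regional difference in mean change (not in the documents), and that the SD and ICC, which are given for mean daily MVPA, also apply to change.

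**1. The plan's own figure.** Design effect 1 + 38 × 0.01 = 1.38; 195/1.38 = 141.3. With 141 per group and student-level degrees of freedom (280), the detectable difference is 5.73 min (5.71 by the normal formula). The stated figure is reproduced.

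**2. Variance of a school mean.** 17.1² × 1.38/39 = 10.35, so the SD is 3.22 min. Of this, 17.1² × 0.01 = 2.92 is between-school variance and 17.1² × 0.99/39 = 7.42 is sampling of students.

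**3. What d does.** Each arm has two city and three regional schools, so d adds 0.4d to both arm means and cancels. The unadjusted and stratum-adjusted differences are identical. The within-arm sum of squares gains 5 × 0.4 × 0.6 × d² = 1.2d²; divided by 4 df, the pooled variance gains 0.3d². With s² the school-level variance within strata, the estimated SE is inflated by √(1 + 0.3d²/s²).

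**4. How large d can be.** Strata split 4:6 contribute 0.4 × 0.6 × d² = 0.24d² to the variance between schools. Even if strata explained all of the 2.92 implied by the ICC, d ≤ √(2.92/0.24) ≈ 3.5 min.

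**5. Size and power.** I compared the t-test (8 df) with the arm-plus-stratum model (7 df) at a true difference of 5.73 min, in simulations of 400,000 trials. There are two ways to introduce d: add it on top of s² = 10.35, or hold the total at 10.35 so that s² = 10.35 − 0.24d² (9.39 at d = 2; 8.19 at d = 3). Where a range is shown, it spans repeated runs.

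| d (min) | variance | SE inflation | type I error, t-test | power, t-test | power, stratum fitted |
|---|---|---|---|---|---|
| 0 | – | 1.00 | 5.0% | 69.5% | 67.7% |
| 2 | d added | 1.06 | 4.0–4.1% | 65–66% | 68% |
| 3 | d added | 1.12 | 3.1–3.2% | 60–61% | 68% |
| 2 | total held | 1.06 | 3.9–4.0% | 69% | 72% |
| 3 | total held | 1.15 | 2.7–2.8% | 69% | 78% |

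With stratum fitted, type I error is 5.0% in every row. Fitting it gains power once d exceeds a value between 1 and 2 min.

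**6. Source of the conservatism.** Under free 5:5 allocation without strata, the same t-test keeps type I error at about 5.0% even at d = 4, a value used here only to test the mechanism. The shortfall therefore comes from pairing a stratified design with an unstratified test.

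**The case against.** The strongest reply is that the protocol's rationale concerns activity levels while the endpoint is change. A constant city–regional difference in level is removed by differencing, and nothing in the documents says that the two-year decline differs by location. This stands: d may be small or zero. In that case the planned test is slightly the better one, and saving one of eight degrees of freedom is defensible.

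A reader might infer much larger losses, for instance power of 54% at d = 4 or 46% at d = 5 when d is added to the planned variance. The documents do not support this. Those values exceed the 3.5 min limit and imply ICCs of about (2.92 + 3.84)/(292.41 + 3.84) = 0.023 and (2.92 + 6.00)/(292.41 + 6.00) = 0.030, against the planned 0.01. With total variance held at the plan's value, the t-test's power does not fall materially; what is lost is the gain available from adjusting.

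A reader might also infer that the precision gained by stratifying is lost altogether, or that false positives rise. Neither follows: the point estimate and its true precision are unchanged, and the test errs towards too few rejections.

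An analysis plan that is not shown could add the stratum term. The protocol nevertheless names the primary test without one, so the two would then need reconciling.

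**Conclusion.** The point holds as a cheap improvement, conditional on the strata differing in mean change. The named test does not match the randomisation, and for any non-zero d its estimated SE is too large on average and its size is below 5%. Within the range the plan's ICC allows, the SE is overstated by about 6% at d = 2 and 12 to 15% at d = 3. The power forgone relative to the adjusted model is about 2 to 3 points at d = 2 and 7 to 9 points at d = 3, against a cost of about 2 points if d = 0. The direction follows from the algebra, given balanced strata. The size rests on an assumed d, on 2:2 and 3:3 allocation, and on applying the plan's SD and ICC to change.

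The 69.5% power at d = 0, below the planned 80%, arises from testing ten school means rather than students. That is a separate matter from the strata.

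**What to change.** Make the primary test a linear model on the ten school-level changes with terms for arm and location stratum (7 residual df), and report the stratum-adjusted difference with its 95% CI. State that blocks are formed within strata, with the resulting 2:2 and 3:3 split. Settle this before outcome data are seen, so that no choice between adjusted and unadjusted results arises later. The cost is one degree of freedom and a change of wording; no further schools, students or measurements are needed.
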